
#### Putative mechanisms

We will pilot the following constructs that have been selected as potential explanatory mechanisms for the hypothesised outcomes of the trial intervention:
The Question of Belonging (QoB) [53] measures the extent to which students feel a part of their university community. The QoB has three items with a 7-point Likert scale, and strong face validity—we will assess the psychometric properties within the present trial. A higher score indicates a greater sense of belonging.The Identification with University (IwU) [54] measures the extent to which students perceive being a university student is consistent with their social identity. The IwU has four items with a 7-point Likert scale, and strong face validity—we will assess the psychometric properties within the present trial. A higher score indicates a greater perception that being a university student is consistent with their social identity.The Domain-Specific Hope Scale social hope (DSHS-sh) and academic hope (DSHS-ah) subscales [55] measure self-agency and pathways thinking in relation to goals pertinent to (respectively) participants’ social relationships and academic study. Both subscales comprise 8 items with an 8-point Likert scale, and both achieve strong internal consistency (Cronbach’s *α* = 0.90) [55]. A higher score indicates greater hope in the respective domain.

#### Participant experience

As part of our aims to assess the acceptability of the UniVRse intervention, we are collecting data on participants’ experience of the intervention and using VR—specifically assessing for both positive experiences and side effects. These outcome measures will only be completed by those participants allocated to the immediate intervention arm:
The Increasing Access to Psychological Therapies Patient Experience Questionnaire (IAPT-PEQ) [56] measures participants’ perception of the intervention they received. The IAPT-PEQ has 8 items using a 5-point Likert scale, each of which is treated as a separate scale. A higher score indicates a more positive intervention experience.The Edinburgh Adverse Effects of Psychological Therapy (EDAPT) [57] measures participants’ experience of side effects after receiving psychological therapy. Of the 42 potential EDAPT items, we have selected 31 items as potentially relevant to this project. Participants indicate whether the side effect applies to them or not (yes or no), and, where yes, rate the severity of the side effect using a 5-point Likert scale. Each item is reported individually with a higher score indicating greater severity of the side effect.The Simulator Sickness Questionnaire (SSQ) [58] measures participants’ experience of side effects after using VR. The SSQ has 16 items with a 4-point Likert scale. Due to concerns regarding the conceptual overlap between the side effects of VR and the symptoms of anxiety, which may lead to measurement error, we will use the revised scoring and factor structure proposed by Bouchard et al. [59], which has demonstrated strong internal consistency (Cronbach’s *α* = 0.87).The Friends and Family Test (FFT) [60] is a single-item measure of patient satisfaction that uses a yes/no response scale. Participants indicate whether they would recommend the intervention to friends and family experiencing a similar difficulty.

In addition to self-report measures of participant experience, we will obtain data from the VR kits to further inform our understanding of participants’ experience of the intervention. We will record the number of sessions completed, the virtual scenarios selected, levels completed within these scenarios, and time spent in VR. We will use these data to report rates of intervention completion, exposure, and dosage, as well as create an overall picture of how participants are using the UniVRse programme.

#### Cortisol

We will be inviting a sub-sample of 15 participants from each arm (30 in total) to provide saliva samples at T0 and T1 to measure levels of the stress hormone cortisol, and any changes in this between timepoints. Participants will be asked to collect their saliva samples, in their domestic setting, using salivettes. They will be asked to provide five samples per day for three consecutive days at T0 and again at T1 – a total of 30 saliva samples across their participation. These samples will need to be provided upon waking, and then 15-, 30-, 45-, and 60-min post awakening. In line with best practice guidance, to monitor sampling accuracy participants will also be asked to wear an activity-monitoring device to bed prior to the three collection days so we can verify the participants’ sleep and wake times [61]. The collection, storage, analysis, and disposal of the saliva samples will adhere to the Human Tissue Act (HTA).

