**Fig. 1 Fig1:**
[figure not shown]
UniVRse trial CONSORT diagram

**Table 1 Tab1:** SPIRIT checklist

	Study period					
	Enrolment	Allocation	Post-allocation			
Timepoint	*-t*_*1*_	0	*T0*	*Intervention*	*T1*	*T2*
Enrolment:						
Eligibility screen	X					
Informed consent	X					
Random allocation		X				
INTERVENTIONS:						
UniVRse programme				X		
Wait list control				X		
ASSESSMENTS:						
T0 assessment			X			
T1 assessment					X	
Exit interviews						X

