### Randomisation and blinding

We will randomise participants to one of the trial arms after they have completed the baseline (T0) assessment. Randomisation will be at a 1:1 group allocation ratio using a permuted blocks algorithm with varying block sizes. The research team will be blinded to the size of the blocks and will have no influence over the outcome of the randomisation. The randomisation sequence will be set up and tested by an independent statistician using Sealed Envelope. The Principal Investigator (PI) will receive notification of each participant’s arm allocation via emails from Sealed Envelope once the T0 assessment has been completed.

Where participants elect to complete the assessments with the support of a research team member, we will ensure that this research team member will be blind to participants’ group allocation. Participants may elect to complete follow-up (T1) assessments independently, meaning they will not be subject to any biases associated with unblinding of the research team. Where T1 assessments are conducted with researcher support, this member of the research team will be blinded to the outcome of the randomisation. If a researcher becomes unblinded before the T1 assessment, a different member of the research team will be allocated to complete the assessment. If blinding is broken during an assessment, then the researcher will cease data collection and contact the PI or offer the participant the opportunity to complete the assessments independently. A different blinded member of the research team will then be allocated to finish the assessment. Any incidents of unblinding will be recorded and reported in any publications.

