Participants will have a degree of flexibility with regard to the session structure of the UniVRse programme, with some fixed parameters. Each session should not exceed 30 min, as being in VR beyond this can cause headaches and eyestrain [39]. Participants will receive a prompt within the virtual environment when they have been using the programme for 30 min. We will give participants access to the VR kit for a month post-randomisation—during this time we recommend that participants complete at least six 30-min sessions. Completing six sessions will constitute completion of the intervention—this is the minimum number of sessions required to complete the introductory psychoeducation, all of the levels in all of the scenarios, and the debrief. We will consider participants to have been ‘exposed’ to the intervention after at least two 30-min sessions. To accommodate the varied schedules of our student participants, they have full control over when they complete these sessions, including the spacing and timing of sessions.

At the start of the UniVRse intervention, participants are presented with a ‘tutorial’ in which Sam gives instruction on how to interact with the virtual environment and provides relevant psychoeducation. Participants are given information on social anxiety, ‘fight or flight’, avoidance as a means of maintaining anxiety, and anxiety habituation. After the tutorial has been completed, participants can select one of four university-based scenarios that they would like to practice being in. The scenarios are: (1) attending a lecture, (2) delivering a presentation, (3) contributing to an online seminar, and (4) group work in a seminar. Within each scenario, there are five graded levels, from the least to most anxiety-inducing. The levels are graded in terms of the number and magnitude of anxiety-related triggers. For example, when in the ‘delivering a presentation’ scenario, the lower levels have a smaller and friendlier-seeming audience, whereas the higher levels have a larger audience that appears more disinterested and includes avatars of teaching staff, with the participant additionally being required to answer a question for which they have not been able to prepare an answer.

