### Data collection and storage

We will utilise a mixed-methods approach to address the project aims. We will collect the quantitative data at baseline (T0) and at a follow-up timepoint of 6 weeks post-randomisation (T1), and qualitative data after the post-randomisation assessment is complete (T2). The quantitative and qualitative data will be combined to understand the acceptability and participant experience of the UniVRse programme and trial.

Participants can choose to complete the assessments either in-person or online and with or without the support of a researcher. The flexibility in our data collection methods is based on patient and public involvement (PPI) feedback. Prior to the T0 assessment, participants will be presented with the participant information sheet (PIS) and asked to complete an eligibility assessment. The eligibility assessment will check whether participants meet the inclusion/exclusion criteria only. Where participants are eligible and interested, they will then be asked to provide written consent before completing the T0 assessment.

Upon completion of the T0 assessment, participants will be randomised to one of the trial arms. Participants will be notified of the outcome of the randomisation via email. The PI will liaise with the participant to arrange access to the UniVRse intervention. After the quantitative data collection is complete, participants in the intervention arm will be invited to complete an exit interview.

Any data that are collected as a hard copy will be scanned at the earliest opportunity and stored electronically on a password-protected university server, and the hard copy will be destroyed. Electronic assessment data will be collected using Qualtrics and then stored electronically on password-protected university computers. Participants will be assigned a unique participant identifier that will be used in place of their name on all assessments. Where data were collected using hard copies, they will be entered into Qualtrics by a member of the research team. We will check the quality of these data by reviewing the concordance between the data entered and the original file for a random sample of 20% of these assessments. Where we find errors in the data entry, we will review the correspondence between the source documents and data entered for the remaining assessments. We will correct any errors identified.

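### The cortisol sub-sample is invited by trial arm for a T0 measure, although arms do not exist until T0 is complete; the sections conflict and leave room for a post-allocation cortisol baseline.

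*Protocol article*

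**What the plan says.** - **Who gives saliva.** The Cortisol section sets the sub-sample by arm: "We will be inviting a sub-sample of 15 participants from each arm (30 in total) to provide saliva samples at T0 and T1".
- **How much.** Sampling takes place at home, with "five samples per day for three consecutive days at T0 and again at T1", described as "a total of 30 saliva samples across their participation". The cortisol baseline therefore occupies three days.
- **When allocation happens.** Randomisation and blinding states: "We will randomise participants to one of the trial arms after they have completed the baseline (T0) assessment". Data collection and storage agrees: "Upon completion of the T0 assessment, participants will be randomised to one of the trial arms". It adds: "Participants will be notified of the outcome of the randomisation via email".
- **When the intervention starts.** The UniVRse section counts kit access from allocation: "We will give participants access to the VR kit for a month post-randomisation".
- **The schedule table.** Table 1 (SPIRIT checklist) places the T0 column after random allocation, under the heading "Post-allocation". The table has no row for cortisol.
- **Eligibility and method.** The Participants section gives the sub-study its own exclusions and lets those excluded stay in the main trial. Allocation is 1:1 in permuted blocks of varying size, with no mention of stratifying by sub-study participation.

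**The concern.** At T0 no participant has an arm, so an invitation issued by arm for a T0 sample cannot be carried out as written. The team can enrol before allocation, in which case the number per arm is an outcome of randomisation and not something it can invite to. Or it can invite after allocation, in which case the T0 saliva is no longer a pre-randomisation baseline. The prose on randomisation points to the first course; the wording of the Cortisol section and the layout of Table 1 point to the second.

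Under the second course two things could go wrong. First, participants would already have been emailed their arm, and those in the intervention arm might already have the VR kit. Cortisol is measured here as a stress hormone, so being wait-listed or starting exposure could plausibly shift the value meant to serve as baseline. Second, agreeing to give 30 samples is a considerable commitment, and people who know their arm may agree at different rates. The two cortisol groups would then no longer be protected by randomisation. Either problem would bias a comparison of T0-to-T1 change between arms, and a baseline taken too late cannot be recovered.

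**Working it through.** **1. The plan's own figures reproduce.** Participants: 15 × 2 = 30. Samples per participant: 5 per day × 3 days × 2 time points = 30. The article gives no power-based size for cortisol, so there is no sample-size formula to check.

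**2. The order of events, side by side.**

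| Place | Order implied |
|---|---|
| Randomisation and blinding | T0, then allocation |
| Data collection and storage | T0, then allocation, then email to the participant |
| Table 1 | allocation, then T0 |
| Cortisol | arm known, then invitation to T0 saliva (literal reading) |

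The first two agree with each other and conflict with the last two.

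**3. Can 15 per arm be met without knowing allocation?** Suppose exactly 30 people enter the sub-study before allocation.

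- *Independent 1:1 allocation (binomial).* P(15/15) = C(30,15)/2^30 = 155,117,520/1,073,741,824 = 0.144.
- *Random 30 out of a 45/45 trial of 90 (hypergeometric).* P(15/15) = C(45,15)²/C(90,30) = 0.177.
- *Permuted blocks, by simulation (4,000 runs per setting).* Block sizes and uptake are assumptions, because the article gives neither. With blocks of 2/4, 4/6 or 4/6/8 and uptake of 50% to 60%, P(15/15) is 0.20 to 0.24. If the first 30 trial entrants all take part, it is 0.72 to 0.89.

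The expected split is 30 × 0.5 = 15 per arm in every case. Near-balance is likely under the two simple models:

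| Split | Binomial | Hypergeometric |
|---|---|---|
| 13/17 or closer | 0.64 | 0.74 |
| 12/18 or closer | 0.80 | 0.88 |

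**4. If 15 per arm is read as a minimum.** Enrolling before allocation until both arms hold at least 15 takes this many people:

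| Setting | Mean | 90th percentile |
|---|---|---|
| Blocks, everyone takes part | 30.1 to 30.3 | 31 |
| Blocks, 50% to 60% uptake | 32.4 to 32.8 | 35 to 36 |
| Simple randomisation | 34.2 | 39 |

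At 50% uptake, just under 2% of simulated trials of 90 did not reach 15 in both arms.

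**5. What an unequal split costs.** With equal variances and complete data, the variance of a difference in means is proportional to 1/n₁ + 1/n₂.

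- 15/15: 1/15 + 1/15 = 0.1333.
- 12/18: 1/12 + 1/18 = 0.1389. The ratio is 1.042, so the standard error rises by about 2%.
- 10/20 (the edge of the 95% binomial range): 1/10 + 1/20 = 0.150. The ratio is 1.125, so the standard error rises by about 6%.

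An exact quota therefore buys very little precision, whereas meeting it by post-allocation selection would risk bias.

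**The case against.** The strongest reply is that the Cortisol wording is shorthand. The article gives the main sample as 45 per arm in the same way, and nobody reads that as selection after allocation. The saliva samples are labelled T0, two sections place T0 before randomisation, and so the natural reading is that saliva comes first. Table 1 concerns the T0 assessment as a whole, has no cortisol row, and may be a labelling slip. The timing of invitations, and whether the saliva days must finish before allocation is released, are details that an article may leave to the full protocol.

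Much of this stands. A reader might infer that 15 per arm is achievable only once allocation is known, or that the quota forces selection after randomisation in more than 80% of cases. The documents support neither. Fifteen per arm may be an expected split. It could be secured by stratifying randomisation on sub-study participation, or reached as a minimum by enrolling about 30 to 34 people on average before allocation. The low probabilities in step 3 concern an exact 15/15 from exactly 30 people, and they depend on blocks and uptake. Nor does any section say that T0 saliva follows randomisation or that people are chosen by arm.

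What does not fall away is the conflict itself. The main-sample figure is a recruitment target, whereas the cortisol sentence describes inviting people from arms to a measurement made before arms exist. Table 1 supports the wrong order. The point rests on statements in the article that disagree, not on missing detail.

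**Conclusion.** The point holds as a conflict that needs correcting, not as proof of a flawed procedure. The invitation by arm and the order in Table 1 cannot both stand beside the two sections that randomise after T0. If staff follow the literal wording, the cortisol baseline could be collected after participants know their arm and entry could depend on arm. If they follow the randomisation sections, neither happens, and 15 per arm is simply the expected split: exact with probability of about 0.14 to 0.24 for a subset, and 12/18 or closer with probability of about 0.80 to 0.88. The 0.20 to 0.24 part of that range rests on assumed block sizes and 50% to 60% uptake. The size of any bias cannot be estimated from the article.

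Severity is moderate. Cortisol is neither a co-primary nor a listed secondary outcome, it appears in none of the three progression criteria, and Planned analysis says that no hypotheses comparing the arms will be tested. The sub-study is still intended to measure change from T0 to T1, and that purpose depends on a clean baseline.

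**What to change.** - **Cortisol section.** Replace the fixed number from each arm with about 30 in total, enrolled before randomisation, with about 15 per arm as a target. Accept the split that results.
- **Randomisation and blinding.** State that, for sub-study participants, sub-study consent and all three T0 saliva days are complete before the allocation is released.
- **Table 1.** Move T0 ahead of random allocation so that the table agrees with the text.
- **Participants already enrolled.** Trial status reports that recruitment opened in January 2024. For each sub-study participant, report whether T0 saliva preceded allocation.

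The cost is a revised paragraph and table, a delay of a few days to randomisation for sub-study participants (three sampling days plus wearing the activity monitor beforehand), and a possibly unequal split, with the small loss of precision shown in step 5. Stratifying randomisation by sub-study participation would bring the split closer to equal, but it means changing a randomisation sequence already in use and is not needed for validity.

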#### Exit interviews

Participants who are randomised to receive the UniVRse intervention will be invited to complete an exit interview to be completed after the T1 assessment. The interview discussion guide combines the Change Interview protocol [62] and trial experience protocols [63] to explore participants’ experience of both the intervention and research procedures. We will invite participants in the intervention arm sequentially to complete an interview, while also trying to ensure this sub-sample is diverse in relation to key participant characteristics. We will cease recruitment when we have reached the recruitment target of 20, meeting sample size recommendations for a larger qualitative study [64].

### Data collection and storage

We will utilise a mixed-methods approach to address the project aims. We will collect the quantitative data at baseline (T0) and at a follow-up timepoint of 6 weeks post-randomisation (T1), and qualitative data after the post-randomisation assessment is complete (T2). The quantitative and qualitative data will be combined to understand the acceptability and participant experience of the UniVRse programme and trial.

Participants can choose to complete the assessments either in-person or online and with or without the support of a researcher. The flexibility in our data collection methods is based on patient and public involvement (PPI) feedback. Prior to the T0 assessment, participants will be presented with the participant information sheet (PIS) and asked to complete an eligibility assessment. The eligibility assessment will check whether participants meet the inclusion/exclusion criteria only. Where participants are eligible and interested, they will then be asked to provide written consent before completing the T0 assessment.

Upon completion of the T0 assessment, participants will be randomised to one of the trial arms. Participants will be notified of the outcome of the randomisation via email. The PI will liaise with the participant to arrange access to the UniVRse intervention. After the quantitative data collection is complete, participants in the intervention arm will be invited to complete an exit interview.

Any data that are collected as a hard copy will be scanned at the earliest opportunity and stored electronically on a password-protected university server, and the hard copy will be destroyed. Electronic assessment data will be collected using Qualtrics and then stored electronically on password-protected university computers. Participants will be assigned a unique participant identifier that will be used in place of their name on all assessments. Where data were collected using hard copies, they will be entered into Qualtrics by a member of the research team. We will check the quality of these data by reviewing the concordance between the data entered and the original file for a random sample of 20% of these assessments. Where we find errors in the data entry, we will review the correspondence between the source documents and data entered for the remaining assessments. We will correct any errors identified.

Cortisol concentrations will be determined by enzyme-linked immunosorbent assay (Salimetrics LLC, State College, PA, USA) at the Psychophysiology and Stress Research Group’s laboratory, University of Westminster. Saliva samples will be destroyed following assay.

The exit interviews will be audio-recorded and transcribed at the earliest opportunity. We will remove any identifying information at the point of transcription and use pseudonyms where necessary. Once the transcripts have been checked for accuracy, the original interview recording will be destroyed. The PI will act as the data custodian and oversee all aspects of data collection, management, and storage. All data procedures will adhere to the General Data Protection Regulation (GDPR) [65].

